## Abstract

**Background:**

Although digital interventions have been widely used in chronic pain management, evidence on their effectiveness has demonstrated heterogeneity. They have low retention rates, which are exacerbated by a lack of feedback, social interaction, and engaging content, contributing to boredom and higher attrition. Gamification offers a possibility to overcome these barriers and enhance user motivation and engagement.

**Objective:**

This study aims to investigate the effects of an online gamified pain management program in a sample of adults with chronic noncancer pain.

**Methods:**

A 2-arm, single-blind randomized controlled trial will recruit 172 participants through Chinese hospitals and online platforms. Eligible participants will be randomized to 2 groups: a 10-week gamified pain management program for the experimental group and routine online pain management materials for the control group. Primary outcomes, including pain intensity and pain interference, and secondary outcomes, including fear avoidance, emotion, exercise adherence, quality of life, and user satisfaction, will be assessed at baseline, after the intervention (10 weeks), and at a 3-month follow-up. A mixed-design ANOVA and intention-to-treat analysis will be used to evaluate intervention effects.

**Results:**

The trial is registered, with recruitment ongoing from July 2025 to August 2026. A total of 172 participants (86 per group) will be recruited. As of November 17, 2025, we have recruited 19 participants. Results are expected to be published in March 2027

**Conclusions:**

The findings will address a critical gap by examining a novel gamified intervention within a theory-driven design to provide an engaging solution to improve self-management in people with chronic pain.

**Trial Registration:**

Chinese Clinical Trial Registry ChiCTR2400094247; https://www.chictr.org.cn/hvshowproject.html?id=266029&v=1.0

**International Registered Report Identifier (IRRID):**

DERR1-10.2196/80542

## Introduction

The Global Burden of Disease Study highlights the substantial prevalence and impact of pain globally [1]. Chronic pain, defined as pain persisting for more than 3 months, significantly affects various aspects of daily life, including work performance, physical activity, and social functioning. It is often associated with psychological disorders such as anxiety and depression, sleep disturbances, substance use, cognitive impairment, and reduced work productivity [2].

Existing guidelines advocate for biopsychosocial treatments that incorporate education, exercise, and psychological interventions to reduce pain in both the short and long term. These approaches emphasize the importance of physical activity and engagement in meaningful daily activities [3,4]. However, the International Association for the Study of Pain has concluded that the training provided to health professionals in pain management is insufficient to achieve effective outcomes [5]. Additionally, patients with chronic pain often face substantial challenges in maintaining physical activity, as they may feel both physically inactive and emotionally hesitant due to the fear of exacerbating pain [6,7].

Online platforms have revolutionized the management of chronic pain by providing accessible alternatives to conventional medical treatments [8]. These platforms allow patients to engage with pain management strategies at their own pace, overcoming barriers such as geographic isolation and socioeconomic disadvantage [9]. Studies suggest that telerehabilitation saves costs and that web-based exercise interventions improve home exercise adherence and confidence [10,11]. Despite their potential, existing online pain management programs often suffer from low retention rates, a problem that is exacerbated by a lack of feedback, social interaction, and engaging content [12]. Gamification has emerged as a promising solution to these challenges, offering an approach that can enhance user engagement by incorporating game elements that motivate and sustain participation [13].

Gamification leverages game mechanics to influence user behavior, improving engagement, motivation, and overall health outcomes [14]. In health care, gamification has proven effective in addressing various health issues and promoting physical activity by making exercise and learning both enjoyable and motivating [15,16]. The use of motivational affordances within gamification has been shown to positively influence psychological factors, such as motivation, attitude, and enjoyment [17], making it a potentially powerful tool for behavior change. Regarding chronic pain, a systematic review demonstrated that gamified exercise interventions, including those using platforms such as Kinect Sport, Nintendo Wii, and virtual reality, can effectively reduce pain by providing interactive scenarios and rewards [18].

Despite these benefits, existing research has not fully explored gamification within the biopsychosocial framework for chronic pain management. Most studies have focused primarily on increasing physical activity, while neglecting the critical educational and psychological components that are essential for comprehensive pain management [18]. As fear of pain is associated with avoidance behaviors, educational interventions, such as those based on pain neurophysiology, can help patients better understand pain and modify their attitudes toward it, potentially leading to improved outcomes [19]. The ability of patients to accept pain sensations, rather than attempting to fight them, has been associated with greater reductions in pain interference [20]. Recent studies have also highlighted the effectiveness of biopsychosocial interventions that combine physical exercise and psychological support to reinforce positive behaviors and challenge negative pain-related perceptions [21,22].

To address this gap in the literature, an online gamified pain management program, based on an escape room task, will be developed and augmented with game elements. The aim of this study is to investigate the effects of online gamified pain management in a sample of adults with chronic noncancer pain via a randomized controlled trial. To this end, the objectives will be to (1) examine the effects of the gamified pain management intervention on the levels of pain intensity, pain interference, psychological outcomes, and quality of life among adults; (2) assess exercise adherence and game experience in the gamified home-based management program; and (3) identify the relationships between the effects of the intervention and sociodemographic factors.

## Methods

### Study Design and Setting

This study is a 2-arm, single-blind (analysts are blinded), randomized controlled trial. A total of 172 individuals with chronic pain will be recruited and randomly assigned to either gamified pain management program (intervention group) or a digital resource package (control group). The interventions for both groups will be delivered online. Participants will complete outcome assessments at 3 time points: baseline (T0), immediately after the intervention (T1), and at a 3-month follow-up (T2). This study protocol follows the SPIRIT (Standard Protocol Items: Recommendations for Interventional Trials) guidelines [23].

### Sample Size

A previous power analysis was used for sample size calculations using G*Power software (version 3.1; Heinrich-Heine-Universität Düsseldorf) [24]. To establish the effect size for the sample size calculation, we synthesized evidence from multiple sources. A meta-analysis analyzing the effects of serious games on pain intensity in patients with chronic pain reported a mean difference of −0.62 (95% CI −1.15 to −0.10) for pain reduction [18]. To supplement this, we conducted another meta-analysis of 12 relevant studies examining the effects of gamification on pain intensity in adults. The results yielded a mean difference of −0.86 (95% CI −1.61 to −0.11) [25-36]. However, given that our digital intervention comprises mixed physical, psychological, and educational components, we also incorporated evidence from 2 other meta-analyses including online pain management and multidisciplinary programs, with effect size of −0.30 (95% CI −0.50 to −0.10) [12] and −0.57 (95% CI −0.63 to −0.50) [37].

Therefore, to ensure robust and conservative statistical power, we selected a medium effect size of 0.50 to reduce potential bias or heterogeneity [38]. The following parameters were used: power (1−β)=0.90, effect size=0.50, and α=.05 (2 tailed). Taking a 20% margin for dropout and missing data, a total of 172 participants will be recruited, with 86 allocated to the experimental group and 86 to the control group.

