### Control Group

In the control group, participants will receive a digital pain management resource package for a 10-week period, containing the same components as the gamified pain management group but delivered in a nongamified, standard digital format. The package contains educational content, exercise videos, educational videos, and relaxation audios that are identical in content and volume to those used in the gamified pain management group, delivered via an online PDF handbook with hyperlinks through WeChat. These multimedia resources are hosted on WeChat and the Xiaohongshu official account to ensure accessibility. In addition, participants will receive interim reminders biweekly via WeChat, encouraging them to read the handbook and engage in exercises, relaxation, and educational activities to promote adherence throughout the intervention period.

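### The stated inputs give 172 with no dropout allowance, so the claimed 20% margin is not supported: a completers' t test after 20% loss has about 83% power, not 90%

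*Protocol article*

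**What the plan says.** All of the calculation is in Methods, Sample Size. The tool is named ("A previous power analysis was used for sample size calculations using G*Power software") and the inputs are listed: "power (1−β)=0.90, effect size=0.50, and α=.05 (2 tailed"). The result follows directly: "Taking a 20% margin for dropout and missing data, a total of 172 participants will be recruited", split 86 and 86. The Abstract repeats it: "A total of 172 participants (86 per group) will be recruited". Procedure and Randomization gives 1:1 allocation. The section does not name the test used in the calculation, and it gives no sample size before the dropout allowance.

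The effect size is justified in these words: "to ensure robust and conservative statistical power, we selected a medium effect size of 0.50". Four sources are cited. Two are described as mean differences in pain, 0.62 for serious games and 0.86 for gamification, with no scale or SD. Two are described as effect sizes: 0.57 for multidisciplinary programmes, and one for online pain management, "with effect size of −0.30 (95% CI −0.50 to −0.10").

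Statistical Analysis plans a mixed-design repeated measures ANOVA by intention to treat, with maximum likelihood for missing values under missing at random.

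**The concern.** A recruitment target that includes a 20% allowance must exceed the number needed for analysis. Here the target equals the number that a standard two-group calculation returns with complete data, so the allowance does not appear in it.

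This matters because the Introduction itself says that online pain programmes retain people poorly, so loss is likely. If the text stands, a null result would be read against a claim of 90% power with dropout already covered, for an effect described as conservative. The article's own figures do not support the dropout part of that claim, and they support the last part only in some of the comparisons it cites.

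**Working it through.** **Inputs.** From Sample Size: d = 0.50, power 0.90, two-sided alpha 0.05, 20% loss. From Procedure and Randomization: 1:1 allocation. Test assumed: two-sample t test, the natural reading of an effect size of 0.50 with a two-tailed alpha in the named software.

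**1. Reproduce the plan's figure.** With n per arm, the noncentrality is d × √(n/2) on 2n − 2 degrees of freedom.
- n = 85: power 89.99%, just short.
- n = 86: 0.50 × √43 = 3.28, power 90.3%.

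The smallest adequate size is 86 per arm, 172 in total. This matches the stated target exactly, with no allowance for loss.

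**2. Add the stated margin.**
- Dividing by the retained fraction: 172/0.8 = 215. By arm, 86/0.8 = 107.5, so 108 per arm and 216 in total.
- Multiplying by 1.2, a common shortcut: 206.4, so 207, or 208 in equal arms.

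Neither gives 172.

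**3. Power at 172 recruited with 20% lost.** 172 × 0.8 = 137.6, about 138, or 69 per arm.
- Noncentrality 0.50 × √34.5 = 2.94; power 83.0%. The type II error rises from about 10% to 17%.
- Effect detectable with 90% power: d = 0.556.

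**4. Other readings of the inputs.**

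| Reading | Before margin | ÷ 0.8 | × 1.2 | Conflict with the text |
|---|---|---|---|---|
| Two-sided, power 0.80 | 128 | 160 | 154 | power is stated as 0.90 |
| Two-sided, power 0.85 | 146 | 183 | 176 | power is stated as 0.90 |
| One-sided, power 0.90 | 140 | 175 | 168 | alpha is stated as two-tailed |
| Repeated-measures between-group test, f = 0.25, 3 measurements, correlation 0.7, power 0.90 | 138 | 172.5 | 166 | no f and no correlation stated |

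Only the last comes close to 172 with a margin, and it needs inputs that the article does not give.

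**5. The effect size.** Taking the four cited values at face value, without sign:

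| Source as labelled | Value | Against 0.50 |
|---|---|---|
| Gamification (mean difference) | 0.86 | larger |
| Serious games (mean difference) | 0.62 | larger |
| Multidisciplinary programmes | 0.57 | larger |
| Online pain management | 0.30 (0.10 to 0.50) | smaller; 0.50 is the far limit of its interval |

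Power at d = 0.30, same t test: 49.9% with 86 per arm and 41.7% with 69 per arm.

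**The case against.** **The margin may have been added to a different calculation.** The planned analysis is a mixed ANOVA over three time points, and the repeated-measures reading above gives 138, then 172.5. A reader might infer from the exact match in step 1 that the margin was certainly never added. The article does not prove that, because it names no test. The t test remains much the likelier reading: it needs no unstated input, and an effect size of 0.50 with a two-tailed alpha fits it. On either reading, the stated inputs do not document the stated margin, and that part stands.

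**The 83% is conditional.** It is the power of a t test on completers at one time point, if the full 20% is lost. The plan keeps partial data through maximum likelihood, which may recover some power. A reader might infer that the trial cannot have 90% power. The documents do not support that; they show only that the stated calculation does not provide it.

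**0.50 was offered as a synthesis of several sources.** It lies below three of the four values, so a flat statement that it is not conservative goes too far. A reader might also convert the two mean differences. On a 0-10 scale with SD 2.0 they would be 0.31 and 0.43, both below 0.50. But scale and SD are assumptions: over SDs of 1.5 to 2.5 the ranges are 0.41 to 0.25 and 0.57 to 0.34, so at SD 1.5 the larger one exceeds 0.50.

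**The contrast is narrow.** The control materials are "identical in content and volume to those used in the gamified pain management group", and a reader might infer that whole-programme effects are too large for this comparison. That is a reason for caution, but the article does not describe the comparators behind the cited estimates, so no figure can be put on it.

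**Conclusion.** The sample-size statement is wrong as written. The stated inputs yield 172 with no loss; with the stated 20% margin they yield 215 to 216. At the plan's own loss rate, a completers' t test has 83% power at d = 0.50, about 7 points below the stated 90%, and 90% power only for an effect of about 0.56. This rests on the two-sample t test, which the article implies but does not name, and on the whole 20% being lost to analysis.

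The effect-size point is secondary and a matter of judgement. The value 0.50 is not conservative against the one estimate labelled online pain management, where power is 50% with 172 analysed and 42% with 138. It is below the other three values at face value, two of which have no scale or SD.

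**What to change.** Keep 172 and correct the text in Sample Size:

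1. Delete the claim that 172 includes a 20% margin. State that 172 gives 90% power with complete data and about 83% with 20% loss, for a two-sample t test at d = 0.50.
2. If a repeated-measures calculation was in fact used, state its f, number of measurements, assumed correlation and the sample size before inflation.
3. Remove the word conservative, or qualify it by reporting power at d = 0.30 (50% and 42%), and give the scale and SD for the two mean differences.

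The cost is a corrected paragraph and a less favourable stated power, with no extra participants. Study Timeline reports 19 recruited by 17 November 2025 and analysis not yet started, so the correction can still be made before any data are analysed. Whether the registry entry repeats the claim cannot be seen from the article and should be checked. Restoring 90% by size alone would mean recruiting 216, which is 44 more.

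Optional: a baseline-adjusted analysis (ANCOVA, or a mixed model with baseline as covariate) could recover power. If the baseline-to-T1 correlation is 0.5, an assumption with no source in the article, the effective d is 0.50/√(1 − 0.25) = 0.577, and power at 69 per arm is about 92%. This changes the planned mixed ANOVA and must be written into Statistical Analysis, not only into the sample-size text. At the same correlation, and with equal variances at both times, change from baseline has variance 2 × (1 − 0.5) = 1 times that of the follow-up score, so a baseline-to-T1 group-by-time contrast gains nothing over the plain t test.

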### Participants and Recruitment

Participants recruitment will be conducted through both on-site and online approaches. A series of offline educational lectures accompanied by recruitment flyers or posters will be held at outpatient pain clinics at Tianhe District People’s Hospital and community service centers in Guangdong province to attract potential participants. Online recruitment will be conducted via social media platforms, including WeChat (version 8.0.66; Tencent Holdings Limited), Xiaohongshu (version 9.14; Xingyin Information Technology Limited), and TikTok (version 6.9.0; ByteDance), by posting advertisements. All recruitment materials will include a brief introduction to the study aim, implementation process, and a survey hyperlink on the Wenjuanxing platform [39] (Ranxing Information Technology Co, Ltd), which will direct participants to the consent form and eligibility screening.

To be eligible to participate in the study, the participants must meet all the following inclusion criteria: (1) be aged 18 years or older, (2) be able to read and understand Mandarin Chinese, (3) own a smartphone with internet access, (4) have a previously diagnosed chronic noncancer pain condition lasting more than 3 months [40], and (5) report a score of ≥2 on the visual analogue scale [41].

Participants will be excluded if they meet one or more of the following exclusion criteria: (1) associated pathologies that make it impossible to perform physical exercise (eg, myopathies, neurological diseases, cardiac diseases, pregnancy, pulmonary diseases, infection, or fracture) [42], (2) undergoing surgery or invasive treatments within the past 3 months [43], or (3) concurrent participation (or participation within the preceding 3 months) in a supervised exercise program or multidisciplinary treatment.

### Procedure and Randomization

The eligibility screening survey will automatically classify individuals after clicking the Agree button as they agree to provide consent. Screening questions will consist of pain intensity, pain duration, health history, recent treatment enrollment, and demographic data. The survey will be designed with conditional logic such that individuals who do not meet the eligibility criteria will be automatically redirected to the end of the survey and prompted to submit their responses. This approach means individuals who are not eligible will neither complete the full survey nor engage in the intervention. Conversely, eligible individuals will proceed to complete the remaining sections, which constitute the full baseline assessment. At the end of the questionnaire, interested participants may provide their WeChat account to receive group allocation and intervention information.

Following baseline assessment, enrolled participants will be randomly assigned in a 1:1 ratio to either the intervention or the control group. A computer-generated randomization sequence using blocks of sizes 2 and 4, stratified by age and sex, will be used. The randomization process will be managed by an independent researcher (JH), and allocation numbers will be stored securely in a password-protected database. Allocation will be revealed to the intervention deliverer ([name], a PhD student) only after a participant is enrolled. The intervention deliverer will be blinded to data assessment and data analysis.

After randomization, participants will be notified of their group allocation and provided with preassigned WeChat log-in credentials. Those in the intervention group will receive a direct message containing a hyperlink to access the gamified pain management platform, while those in the control group will receive a digital resource package. After the intervention, T1 (10 weeks immediately after intervention) and T2 (3-month follow-up) assessments will be collected via the Wenjuanxing platform [39], and semistructured interviews will be conducted to collect individual’s perceptions and experiences of the intervention. Participants who report the most, moderate, or least change in pain intensity will be invited to participate in the interviews.

### Study Intervention

The design of the gamified pain management is based on established gamification principles and frameworks [44,45] and is theoretically grounded in self-determination theory (SDT), which supports individual autonomy, competence, and relatedness to improve intrinsic motivation and sustain engagement [46]. The intervention was co-designed by an expert in chronic pain ([name]) and an expert in digital health ([name]), with contributions from the lead researcher (JH), a pain clinic clinician, a physiotherapist with more than 5 years of experience, and 3 internet technology specialists. The intervention is delivered via the web-based platform VxEditor [47], which is accessible on both smartphones and computers, over a maximum of 10-week period, allowing participants to complete the program at their own pace. In addition, participants can choose their specific pain site via the platform, which tailors exercises accordingly and thus improve autonomy.

The gamified pain management is designed as an “escape room” game. Participants assume the role of a hero (avatar) guiding others to escape from a metaphorical “pain room,” which fosters a sense of relatedness. The intervention consists of 8 core “rooms” (sessions). Participants must complete various challenges, including unlocking 10 clues and accumulating at least 60 points to progress from one session to the next, which is designed to foster a sense of competence. Participants are awarded 5 points for completing each exercise task and 2 points for correct quiz answers, while skipping an exercise earns no points. To further support competence and reinforce the knowledge of pain, immediate and automatic feedback is provided, offering affirmation and encouragement for correct quiz answers and explanatory feedback for incorrect answers. Four optional hidden sessions are also available, offering additional challenges for highly engaged users. A detailed overview of the gamification design is provided in Table 1.

**Table 1 table1:** Gamification design of the interventions.

Game elements	Applicable gamified interventions
Anonymity	Users are anonymized and represented by a unique code.
Avatar	Users assume the role of a hero (avatar) in the game.
Narrative	A background story (escape from the pain room) is presented to engage users.
Tutorials	Introductory tutorials establish an emotional connection with users and provide step-by-step instructions.
Choices	Users can select different games based on their specific pain site.
Feedback	Users receive notifications upon completion of exercises and correct quiz answers.
Points	Users earn points for completing exercises and quizzes and for progressing to the next sessions.
Progression and leaderboard	A progress number indicates the level of effort achieved.
Challenges and rewards	Completing challenges unlocks hidden games with additional exercise opportunities.

The contents of the intervention consist of exercises complemented with education and relaxation practices, which are identified as “clues” within each session. Education topics are presented through animated videos and written notes, focusing on pain mechanisms, neurobiology and neurophysiology, the biopsychosocial model of pain, and management strategies [48]. Quizzes are used to assess and reinforce knowledge from the educational content. A total of 28 prerecorded exercise videos demonstrate stretching, strengthening, balance, and resistance exercises [49], tailored to specific pain areas (eg, neck, shoulder, back, knee, or head). The program recommends at least 60 minutes of exercise per week, and the completion of each exercise is verified via an in-video dialogue prompt that appears midway through the video, which participants must click to earn points. The relaxation practices are presented through recorded audios that guide participants in breathing exercises and muscle relaxation [50]. In addition, participants are required to solve real-world case puzzles by applying their knowledge to determine the mechanisms of chronic pain, which is a key task for session completion. Details of these components are shown in Table 2.

**Table 2 table2:** The gamified pain management intervention components.

Session	Clue components
1	Exercise: three 6-minute balancing exercises Educational information: pain mechanisms Relaxation audio: breathing exercises Quiz and puzzle
2	Exercise: three 6-minute stretching exercises for different pain sites Educational information: etiology of pain Relaxation audio: breathing exercises Quiz and puzzle
3	Exercise: three 6-minute core strengthening exercises Educational information: neurobiology and neurophysiology of pain Relaxation audio: muscle relaxation Quiz and puzzle
4	Exercise: three 6-minute stretching exercises for different pain sites Educational information: biopsychosocial model of chronic pain Relaxation audio: muscle relaxation Quiz and puzzle
5	Exercise: three 6-minute core strengthening exercises Educational information: attention system and pain and distraction from pain Relaxation audio: body scan Quiz and puzzle
6	Exercise: three 6-minute balancing exercises for different pain sites Educational information: medication use and drug abuse Relaxation audio: body scan Quiz and puzzle
7	Exercise: three 6-minute core strengthening exercises Educational information: physical activity for chronic pain Relaxation audio: relaxation music Quiz and puzzle
8	Exercise: three 6-minute resistance exercises Educational information: nonpharmacological strategies Relaxation audio: outdoor relaxation Quiz
Four hidden sessions	Exercise: three 20-minute stretching and resistance exercises

The gamified pain management platform automatically captures and stores detailed engagement data on a secure, cloud-based back end. The latest room successfully completed is recorded, allowing research staff to track progress. Time stamps for the first log-in and last interaction with the platform are also generated to calculate the total time spent. Quiz accuracy rates and total points accumulated are stored on the backend, enabling monitoring by the research team. To promote adherence, interim reminders will be sent via WeChat biweekly to participants who have not progressed at the expected pace. After completing the program, participants are encouraged to continue using the platform for practice. Screenshots of the gamified pain management are provided in Figures 1-4.

